### **1.3 Potential Risks and Benefits**

#### **1.3.1 Known Potential Risks**

Any drug or therapy at any stage of the study may present unforeseen and potentially severe toxicities and adverse effects. The primary risk for patients with chemotherapy-induced nausea and vomiting is the impact on food intake. For patients requiring radical concurrent chemotherapy for their tumors, CINV can lead to a decline in quality of life and physical function, resulting in reduced chemotherapy doses, delayed chemotherapy, or even termination of chemotherapy, thereby affecting the anti-tumor treatment process and efficacy, and potentially increasing mortality.

The current guidelines recommend a multimodal regimen for preventing nausea and vomiting induced by moderately to highly emetogenic chemotherapy, typically including a 5-HT3 RA, an NK-1 RA, and multi-day dexamethasone, with or without olanzapine. Although DEX has been used as part of the classic antiemetic regimen for many years, its associated side effects should not be overlooked. Vardy JL et al. conducted a survey on the side effects of dexamethasone for preventing CINV, summarizing moderate to severe adverse reactions including insomnia (45%), gastrointestinal symptoms (27%), anxiety and irritability (25%), increased appetite (18%), weight gain (17%), rash (15%), depression after discontinuation of treatment (7%), hiccups (7%), and oral candidiasis (3%). Among the 60 patients receiving MEC who participated in this survey, only 15 patients (25%, 95% CI 15-38%) reported no

side effects or only mild side effects, while 19 patients (32%, 95% CI 20-45%) reported at least three moderate to severe symptoms [13]. Given the high rate of reported symptoms, these side effects may outweigh the benefits of dexamethasone when used with moderately emetogenic chemotherapy. Another review also pointed out that corticosteroid therapy may lead to side effects such as metabolic abnormalities, central nervous system effects, glaucoma, cataracts, acne, impaired wound healing, dyspepsia, myopathy, hypertension, increased risk of infection, or hypothalamic-pituitary-adrenal axis suppression [14]. A dose-dependent sensation of perineal itching lasting several minutes after dexamethasone administration has also been reported in clinical trials [15].

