## **8.4 Adverse Events (AEs)**

### **8.4.1 Definition of Adverse Events**

An adverse event is any untoward medical occurrence in a participant in a clinical trial after signing the informed consent form, but it does not necessarily have a causal relationship with the study drug. An adverse event can be any unexpected, unfavorable symptom, sign, disease, or abnormal laboratory finding, regardless of whether it is related to the study drug. Adverse events include the following situations: 1) pre-existing medical conditions/diseases before the start of study treatment, which are only considered adverse events if they worsen after the initiation of the study drug; 2) any new adverse events; 3) abnormal laboratory values or findings, which are considered adverse events only if they are deemed clinically significant.

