### **8.4.3 Criteria for Assessing the Relationship Between Adverse Events and the Study Drug**

All adverse events, including any unexpected clinical manifestations that occur after signing the informed consent form, regardless of whether they are related to the study drug or even whether the drug was administered, should be reported as adverse events. All adverse events must be reported in the form of a clinical report. Any discomfort reported by the patient during the treatment period or any abnormal changes in objective laboratory test indicators should be accurately recorded, along with the severity, duration, management measures, and outcomes of the adverse events. Investigators should also comprehensively assess the relationship between adverse events and the study drug, using a five-category classification method to evaluate the potential association between adverse events and the study medication: "definitely related," "probably related," "probably not related," "definitely not related," and "unable to determine." "Definitely related," "probably related," and "unable to determine" are all classified as drug adverse reactions. When calculating the incidence of adverse events, the sum of these two categories is used as the numerator, and the total number of participants used for safety evaluation is used as the denominator. The criteria for judgment are as follows:

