**Table 2: Criteria for Assessing the Relationship Between AEs and the Investigational Drug**

| Category             | Criteria                                                                                                                                                                                                                                                                                                            |
|----------------------|---------------------------------------------------------------------------------------------------------------------------------------------------------------------------------------------------------------------------------------------------------------------------------------------------------------------|
| Definitely Related   | The event occurs within a plausible time frame after drug administration, aligns with the known reaction profile of the drug, improves upon discontinuation, and recurs upon re-administration.                                                                                                                     |
| Possibly Related     | The event occurs within a plausible time frame after drug administration but does not align with the known reaction profile of the drug. The subject's clinical condition or other treatments may also contribute.                                                                                                  |
| Possibly Unrelated   | The event does not occur within a plausible time frame after drug administration and does not align with the known reaction profile of the drug. The subject's clinical condition or other treatments may contribute.                                                                                               |
| Definitely Unrelated | The event does not occur within a plausible time frame after drug administration and does not align with the known reaction profile of the drug. The subject's clinical condition or other treatments are likely the cause, and the event resolves with disease improvement or discontinuation of other treatments. |
| Unable to Determine  | The event's timing relative to drug administration is unclear, and it resembles the known reaction profile of the drug or could be caused by concomitant medications.                                                                                                                                               |

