**Dexamethasone for injection and oral NEPA**

**XMZSY-AP-SC-12-03**

**<Version 2.0>, <Version Date June 10, 2024>**

|                                                      |                                                                                                                                                                                                                |                                                                                                                                                                                                            |
|------------------------------------------------------|----------------------------------------------------------------------------------------------------------------------------------------------------------------------------------------------------------------|------------------------------------------------------------------------------------------------------------------------------------------------------------------------------------------------------------|
| Actions Taken for Investigational Drug               |                                                                                                                                                                                                                |  Continued Use  Dose Reduction  Drug Suspended then Resumed  Drug Discontinued                             |
| SAE Outcome                                          |  Symptoms Disappeared (With/Without Sequelae)  Symptoms Persist  Death (Time of Death:        )                                        |                                                                                                                                                                                                            |
| Relationship Between SAE and Investigational Drug    |                                                                                                                                                                                                                |  Definitely Related  Possibly Related  Possibly Unrelated  Unrelated  Unassessable |

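### Section 8.4.3 computes the incidence of adverse events from relatedness categories only and sums two categories after naming three; Table 2 pushes known dexamethasone effects towards the category left in doubt

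*Protocol*

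**What the plan says.** Section 8.4.1 defines an adverse event as any untoward occurrence after consent, "regardless of whether it is related to the study drug". Section 8.4.3 opens with the same all-cause rule.

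Section 8.4.3 then sets up a five-level causality scale and says that three of its levels, *definitely related*, *probably related* and *unable to determine*, "are all classified as drug adverse reactions". The next sentence fixes a rate: "When calculating the incidence of adverse events, the sum of these two categories is used as the numerator". Its denominator is everyone evaluated for safety.

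Table 2 gives the criteria for each level. *Definitely Related* needs plausible timing, agreement with the known reaction profile, and that the event "improves upon discontinuation, and recurs upon re-administration". *Possibly Related* reads: "The event occurs within a plausible time frame after drug administration but does not align with the known reaction profile of the drug", with the patient's condition or other treatments as possible contributors.

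Treatment-related adverse events are a secondary safety endpoint (Synopsis; section 2.2.3). Section 10.6 lists the incidence and severity of adverse events as one item and the analysis of their relationship to the drug as another, with no formula for either.

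**The concern.** Two things in the rule do not agree with their surroundings.

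- **The label.** A rate called the incidence of adverse events is built only from events judged related or unassessable. Followed literally, it drops every event rated unrelated, although 8.4.1 makes those adverse events on the same footing.
- **The count.** Three categories are named and two are summed, and the sentence does not say which two.

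Safety is the trial's secondary objective, and section 1.3.1 justifies the step from 8 mg to 5 mg by the hope of fewer and milder dexamethasone side effects. A reader who meets a reported incidence of adverse events should know whether it is all-cause or related only. If it is related only, the reader should also know whether unassessable events are in it. The protocol as written permits different answers. Because the trial is open-label (section 10.2), the choice would be made by people who know the allocation, unless it is settled beforehand.

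**Working it through.** The rule rests on no stated figure, so there is nothing to reproduce. The check sets the sections side by side.

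**1. All-cause or related?** Section 8.4.1 and the first sentence of 8.4.3 make relatedness irrelevant to being an adverse event. The numerator later in 8.4.3 consists of relatedness categories only. Both cannot describe the same quantity. The numerator suits the treatment-related endpoint in 2.2.3, so the likeliest explanation is an adverse-reaction rate under the wrong name.

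**2. Two or three?** Three categories are named immediately before the sum of two. One reading is that *two* is a stale count and all three belong. Another is that the sum covers the two *related* levels and leaves out *unable to determine*. The first is likelier, because the sentence before treats all three alike, but the text does not decide it.

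**3. Where does a typical dexamethasone effect land in Table 2?** Take insomnia, the most frequent symptom (45%) in the survey cited in section 1.3.1, starting soon after the dose.

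| Row | Fits? | Reason |
|---|---|---|
| Definitely Related | Rarely | Needs recurrence on re-administration. Section 5.2.1 gives each drug once before chemotherapy, and section 10.2 describes a single-cycle observation. |
| Possibly Related | No | Needs the event not to match the known profile; insomnia does match. |
| Possibly Unrelated | No | Needs implausible timing and a mismatch with the profile. |
| Definitely Unrelated | No | Same two conditions. |
| Unable to Determine | Only on one reading | Asks for unclear timing together with resemblance to the profile. If its last clause, on concomitant medication, stands alone, an event that chemotherapy could also cause may be placed here. |

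Such an event has no clear home, and the only row open to it without re-challenge is the one that step 2 leaves in doubt. I say *rarely* for the first row because section 1.3.1 mentions a second treatment cycle for some patients, although the objectives, design and dosing sections do not carry it.

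**4. What depends on the answer?** Place each participant in one arm once, at the strongest category reached. Let D, P and U be the numbers at *definitely related*, *probably related* and *unable to determine*. Let R be the number with unrelated events only, and N the number evaluated for safety.

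- Two categories: (D + P)/N
- Three categories: (D + P + U)/N
- All-cause: (D + P + U + R)/N

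The gaps between readings are U/N and R/N. With all 93 randomised participants of an arm in the safety set (section 10.1), each participant in U or R moves the rate by 1/93 = 1.08 percentage points. The protocol gives no value for U or R in either arm, so the gaps cannot be sized.

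**The case against.** The best defence is that this is a slip of wording. The preceding sentence puts all three categories together, so *two* is naturally read as *three*. A related-only numerator is what the treatment-related endpoint needs, so only the name is wrong. Sections 8.4.1, 8.4.3 and 8.4.4 require every event to be recorded whatever its cause, so nothing is lost. Most of this stands: the data will be complete and the likely intention can be guessed. It does not remove the point, because the protocol fixes the formula itself, and an analysis plan that follows it must either guess or depart from it.

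Some stronger readings are tempting, and the documents do not support them.

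- **That 8.4.3 contradicts section 10.6, or that all-cause incidence will not be reported.** Section 10.6 gives no formula and lists incidence apart from relatedness. It is compatible with an all-cause analysis and is not itself contradicted.
- **That the rate is meaningless because the numerator has no unit.** Counting events or participants is ordinary detail for a statistical analysis plan. With a denominator of participants, participants with at least one event is the natural reading.
- **That the naming differences make separate scales.** *Probably* in the text, *Possibly* in Table 2, and *Unassessable* under "Relationship Between SAE and Investigational Drug" on the report form are variants of the same five levels. They are clerical.
- **That the cited survey sizes the problem.** It reports symptoms from another setting and says nothing about how investigators here will attribute events.

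The Table 2 argument also has a limit. On the looser reading of its last row, a known effect is placed there and, if all three categories count, it is counted.

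**Conclusion.** The point holds in a limited form. The rule in 8.4.3 is wrong as written on two counts: it names a relatedness-based rate as the incidence of adverse events, and it sums two categories out of three. Table 2 makes the second more than a typing error, since the events that the lower dose is meant to reduce fit neither related row well and may fall into the category whose inclusion is unclear.

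The effect on any reported rate is unknown, in size and in direction between arms. That the numerator was meant as a treatment-related rate is my inference from its content and from 2.2.3. The primary endpoint, its non-inferiority test and the sample size are unaffected, and the correct rates can be computed from what is collected. It should be corrected before analysis, but it does not threaten the trial's main conclusion.

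**What to change.** - **Section 8.4.3.** Rename the rate *incidence of adverse drug reactions (treatment-related AEs)*. Replace the reference to two categories with the three by name (*definitely related*, *possibly related*, *unable to determine*), worded as in Table 2, over the safety set described in section 11.
- **Section 10.6.** State that the incidence of adverse events is reported regardless of causality, by arm, beside the treatment-related rate.
- **Table 2.** Let *Possibly Related* also cover events with plausible timing that match the known profile but were not re-challenged.

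The unit (participants with at least one such event) can be added in the same edit or left to the statistical analysis plan.

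The cost is a few sentences and one table row, with no new data. All-cause rates will include chemotherapy toxicity and may dilute a dexamethasone effect, which is why both rates are worth showing. The change does not remove the influence of open-label attribution on the treatment-related endpoint.

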**Table 2: Criteria for Assessing the Relationship Between AEs and the Investigational Drug**

| Category             | Criteria                                                                                                                                                                                                                                                                                                            |
|----------------------|---------------------------------------------------------------------------------------------------------------------------------------------------------------------------------------------------------------------------------------------------------------------------------------------------------------------|
| Definitely Related   | The event occurs within a plausible time frame after drug administration, aligns with the known reaction profile of the drug, improves upon discontinuation, and recurs upon re-administration.                                                                                                                     |
| Possibly Related     | The event occurs within a plausible time frame after drug administration but does not align with the known reaction profile of the drug. The subject's clinical condition or other treatments may also contribute.                                                                                                  |
| Possibly Unrelated   | The event does not occur within a plausible time frame after drug administration and does not align with the known reaction profile of the drug. The subject's clinical condition or other treatments may contribute.                                                                                               |
| Definitely Unrelated | The event does not occur within a plausible time frame after drug administration and does not align with the known reaction profile of the drug. The subject's clinical condition or other treatments are likely the cause, and the event resolves with disease improvement or discontinuation of other treatments. |
| Unable to Determine  | The event's timing relative to drug administration is unclear, and it resembles the known reaction profile of the drug or could be caused by concomitant medications.                                                                                                                                               |

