### **2.2 Research Indicators**

#### **2.2.1 Primary Endpoint**

Proportion of subjects with complete response (defined as no vomiting and no rescue medication within 7 days after receiving the study drug).

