## 4.2 Exclusion Criteria

Subjects with any of the following conditions are not eligible for this study:

1. Received radiotherapy within one week before chemotherapy.
2. Suffer from other diseases that cause nausea or vomiting except those caused by tumor chemotherapy drugs, including but not limited to gastrointestinal obstruction and central nervous system malignancies.
3. Experienced vomiting, nausea, or mild nausea within 24 hours before treatment.
4. Concurrent use of corticosteroids or any other possible antiemetic drugs.
5. Contraindications to corticosteroids.
6. Cognitive impairment (such as dementia or severe learning difficulties) that prevents completion of nausea and vomiting-related evaluation scales, etc.
7. Use of antipsychotic drugs within 30 days before the start of treatment or during treatment.
8. Severe and uncontrolled diseases affecting the liver, kidneys, cardiovascular, respiratory, endocrine systems, or the central nervous system.
9. Allergy to the study drugs.
10. Pregnant or lactating women.
11. Participated in any other clinical study of investigational drugs or devices within three months before screening.
12. The investigator deems that participation in the trial poses a significant risk to the subject's health or safety or may affect the assessment of efficacy for other reasons.

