# 8 Safety Evaluation

Safety evaluation includes the recording of adverse events (AEs) and serious adverse events (SAEs) from the time participants sign the informed consent form until the end of the study, through vital signs, physical examination, laboratory tests, electrocardiogram, echocardiogram, abdominal ultrasound, etc. The safety of the study drug is evaluated according to the Common Terminology Criteria for Adverse Events (CTCAE) version 5.0, and the incidence and severity of nausea and vomiting events are recorded in accordance with the NCCN (2024.V1) Clinical Practice Guidelines. Participants should be closely monitored for changes in symptoms and signs after drug administration during the study. Any AEs that occur should be promptly managed to ensure the safety and well-being of the participants. After timely management of AEs, their diagnosis (or symptoms if no diagnosis is made), onset and resolution dates, severity, relationship to the study drug, whether treatment was required, management measures, and outcomes should be recorded, followed by analysis, evaluation, and statistical analysis of the AEs.

All participants must undergo comprehensive physical and laboratory examinations during the study, including measurement of temperature, pulse, respiration, blood pressure, complete blood count, urine routine, biochemical profile,

coagulation function, 12-lead electrocardiogram, echocardiogram, and abdominal ultrasound. If clinically significant abnormal changes occur, they should be closely monitored and managed until they return to normal or baseline levels or stabilize.

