## **8.3 Nausea and Vomiting Assessment**

Investigators will record the incidence and severity of nausea and vomiting events according to the NCCN (2024.V1) and CTCAE (V5.0) Clinical Practice Guidelines.

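### The causality rules leave no way to rate plausibly timed chemotherapy-induced vomiting as unrelated, so the treatment-related AE endpoint can overlap with primary-endpoint failure and dilute a true safety difference

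*Protocol*

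**What the plan says.** The Protocol defines adverse events broadly in section 8.4.1: "An adverse event is any untoward medical occurrence in a participant in a clinical trial after signing the informed consent form". Section 8.4.3 adds that "Any discomfort reported by the patient during the treatment period or any abnormal changes in objective laboratory test indicators should be accurately recorded". Under section 8, Safety Evaluation, "the incidence and severity of nausea and vomiting events are recorded in accordance with the NCCN (2024.V1) Clinical Practice Guidelines", and section 8.3 adds CTCAE grading. Section 4.2 excludes anyone who "Experienced vomiting, nausea, or mild nausea within 24 hours before treatment", so vomiting on study is a new event.

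Table 2 gives the criteria for causality. *Possibly Related* reads: "The event occurs within a plausible time frame after drug administration but does not align with the known reaction profile of the drug", with the patient's condition or other treatments as possible contributors. *Possibly Unrelated* and *Definitely Unrelated* both require that the event falls outside a plausible time frame and is off-profile. Section 8.4.3 says that definitely related, probably related and undeterminable events "are all classified as drug adverse reactions".

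The primary endpoint in section 2.2.1 is "no vomiting and no rescue medication within 7 days after receiving the study drug". Treatment-related AEs are a secondary safety endpoint in section 2.2.3 and in the synopsis, with no separate definition of treatment-related.

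**The concern.** Section 1.3.1 gives the rationale: keep control of nausea and vomiting at 5 mg dexamethasone while reducing adverse reactions. It also concedes that control may be worse at 5 mg. For the two claims to be judged separately, the safety endpoint must not move with the efficacy endpoint.

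Read literally, the causality rules let vomiting caused by chemotherapy enter the treatment-related AE numerator. With equal efficacy, shared events can blur the safety contrast. If efficacy is somewhat lower at 5 mg, the extra failures offset a real reduction in steroid effects, and a reader of the AE table could not tell the two apart.

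**Working it through.** **Step 1: apply Table 2 to one case.** A patient vomits a few hours after chemotherapy. By section 5.2.1 dexamethasone was given 0.5 h, and the capsule 1 h, before chemotherapy.

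- *Possibly Unrelated* and *Definitely Unrelated*: both need implausible timing. The timing is plausible, so neither applies, however obvious chemotherapy is as the cause.
- *Unable to Determine*: needs unclear timing. The timing is known.
- *Definitely Related*: needs an on-profile event that recurs on re-administration. This is a single dose observed over a single cycle (section 10.2).
- *Possibly Related*: plausible timing, off-profile, other treatments may contribute. This is the best fit, and it is the second of the five categories, which section 8.4.3 counts as a drug adverse reaction.

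No sentence exempts efficacy events. The protocol does write an exemption elsewhere: section 8.5.2 removes disease progression from SAE reporting.

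**Step 2: the plan's own figures.** The protocol gives no figure for treatment-related AEs. Its sample size reproduces: 88 per group with 80% in both arms, margin 15 points, one-sided alpha 0.05, power 80%, unpooled. That is 176 in total, and 176 / 0.95 = 185.3, rounded up to 186. The sample size is not affected by this point.

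**Step 3: size of the overlap.** Inputs: complete response rate (CRR) 80% at 8 mg (section 10.1); 5 mg CRR varied from 80% down to 65%, the margin. Assumed, not in the documents: rates of other related AEs p = 25% (5 mg) and 35% (8 mg); independence of failures and other AEs; a share s of failures logged as related AEs.

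P(any counted event) = 1 - [1 - s(1 - CRR)] x (1 - p)

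With s = 1 this is 1 - CRR x (1 - p). At 8 mg: 1 - 0.80 x 0.65 = 48.0%. At 5 mg and CRR 70%: 1 - 0.70 x 0.75 = 47.5%.

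With s = 0.5, at 8 mg: 1 - 0.90 x 0.65 = 41.5%. At 5 mg and CRR 65%: 1 - 0.825 x 0.75 = 38.1%.

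| CRR at 5 mg | 5 mg, all logged | Difference from 48.0% | 5 mg, half logged | Difference from 41.5% |
|---|---|---|---|---|
| 80% | 40.0% | -8.0 | 32.5% | -9.0 |
| 75% | 43.8% | -4.3 | 34.4% | -7.1 |
| 70% | 47.5% | -0.5 | 36.3% | -5.3 |
| 65% | 51.3% | +3.3 | 38.1% | -3.4 |

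The true difference is -10 points throughout.

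**Step 4: sensitivity.**

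- *Overlap, all failures logged.* If no patient has both kinds of event, rates add: 8 mg 35 + 20 = 55%, 5 mg 25 + failures, so the differences are -10, -5, 0 and +5 points. If overlap is maximal, the larger rate applies: 8 mg 35%, 5 mg 25, 25, 30 and 35%, so the differences are -10, -10, -5 and 0.
- *Other assumed rates (independent, all logged).* With 20% vs 30%, the 10-point benefit becomes 8, 4 and 0 points, then a 4-point reversal at 65%. With 30% vs 45%, a 1.5-point benefit remains at 65%. With a smaller true benefit, 25% vs 30%, the sign has already turned by 3.5 points at a CRR of 70%.

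**The case against.** The strongest reply is that the protocol never says vomiting is a drug adverse reaction. That is right: the result follows from reading four places together. Investigators are asked to assess causality comprehensively, *plausible time frame* is undefined, and vomiting at 120-168 h after one dose might reasonably be called implausibly timed. Section 1.3.1 lists gastrointestinal symptoms among dexamethasone reactions, so a rater might treat vomiting as on-profile and outside *Possibly Related*. These points limit how often the overlap would occur. They do not remove it: an on-profile event still cannot be rated unrelated, because both unrelated rows also require the event to be off-profile. Departing from Table 2 leaves the rating to discretion in an open-label trial.

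It can also be said that section 8.3 is separate from 8.4, that nausea grading is needed for the exploratory complete control rate, and that handling of efficacy events in AE tables often belongs in the SAP or CRF guidance. The placement of 8.3 is indeed no evidence of error. But the AE definition, causality table and counting rule are all stated in the protocol, and the fault lies in them.

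The consequence is bounded. Section 10.6 names no between-arm test of treatment-related AEs, a tabulation by AE term would show vomiting separately, and the glucose and ECG endpoints are untouched.

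A reader might infer that the trial will count every emetic failure as a drug reaction and so reverse the safety result. The documents do not support that. Actual logging is unknown, and a failure by rescue use alone need not produce an AE record.

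**Conclusion.** The point holds as a fault in the stated rules: plausibly timed chemotherapy-induced vomiting cannot be rated unrelated under Table 2, best fits a category counted as a drug adverse reaction, and can therefore overlap with failure on the primary endpoint. Linking that classification to the treatment-related AE endpoint is an inference, made because no other definition is given.

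The main effect is dilution. With assumed rates of 25% vs 35%, independence and full logging, a 10-point benefit falls to about 8 points at equal 80% CRR and to about 0 at a 5 mg CRR of 70%. At those rates reversal needs a CRR near 65% and almost complete logging; with half logged at 65%, a 3.4-point benefit remains. Under either extreme of overlap there is no dilution at equal CRR, and under maximal overlap no reversal even at 65%. These sizes rest on AE rates the documents do not give. The correction should be made, but the primary analysis is unaffected.

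**What to change.** - In section 8.4.3, state that nausea and vomiting from study drug to 168 h are efficacy outcomes, excluded from the treatment-related AE numerator. Show the rates including them alongside.
- Keep recording these events, as section 8.4.3 requires, and report them as SAEs whenever they meet section 8.5.1. Removing them from the AE record would conflict with the recording rule.
- Revise Table 2 so that a plausibly timed event with a clear alternative cause can be rated unrelated, and an on-profile event can be rated possibly related. At present a well-timed, on-profile dexamethasone effect fits neither related row: *Possibly Related* requires it to be off-profile, and *Definitely Related* requires recurrence on re-administration.
- Reconcile *probably* in the text with *Possibly* in the table, and the numerator's two categories with the three just named.

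The cost is a few sentences, a revised table and a matching CRF completion note. Headline treatment-related AE rates will be lower and need a footnote. Section 8.3 need not be moved.
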